## 12.2 SF-36 questionnaire

### 12.2.1 SF-36 questionnaire Chinese version

## SF-36 量表

请用画圈“√”的形式，选择符合您目前状态的内容。谢谢您的配合！

1、总体来讲，您的健康状况是：

- ①非常好    ②很好    ③好    ④一般    ⑤差

2、跟1年以前比您觉得自己的健康状况是：

- ①比1年前好多了    ②比1年前好一些    ③跟1年前差不多

- ④比1年前差一些    ⑤比1年前差多了

### 健康和日常活动

3、以下这些问题都和日常活动有关。请您想一想，您的健康状况是否限制了这些活动？如果有限制，程度如何？

（1）重体力活动。如跑步举重、参加剧烈运动等：

- ①限制很大    ②有些限制    ③毫无限制

（2）适度的活动。如移动一张桌子、扫地、打太极拳、做简单体操等：

- ①限制很大    ②有些限制    ③毫无限制

（3）手提日用品。如买菜、购物等：

- ①限制很大    ②有些限制    ③毫无限制

（4）上几层楼梯：

- ①限制很大    ②有些限制    ③毫无限制

（5）上一层楼梯：

- ①限制很大    ②有些限制    ③毫无限制

**(6) 弯腰、屈膝、下蹲:**

①限制很大    ②有些限制    ③毫无限制

**(7) 步行 1500 米以上的路程:**

①限制很大    ②有些限制    ③毫无限制

**(8) 步行 1000 米的路程:**

①限制很大    ②有些限制    ③毫无限制

**(9) 步行 100 米的路程:**

①限制很大    ②有些限制    ③毫无限制

**(10) 自己洗澡、穿衣:**

①限制很大    ②有些限制    ③毫无限制

**4、在过去 4 个星期里，您的工作和日常活动有无因为身体健康的原因而出现以下这些问题？**

**(1) 减少了工作或其他活动时间:**

①是    ②不是

**(2) 本来想要做的事情只能完成一部分:**

①是    ②不是

**(3) 想要干的工作或活动种类受到限制:**

①是    ②不是

**(4) 完成工作或其他活动困难增多（比如需要额外的努力）:**

①是    ②不是

**5、在过去 4 个星期里，您的工作和日常活动有无因为情绪的原因（如压抑或忧虑）而出现以下这些问题？**

**(1) 减少了工作或活动时间:**

①是    ②不是

**(2) 本来想要做的事情只能完成一部分:**

①是    ②不是

**(3) 干事情不如平时仔细:**

①是    ②不是

**6、在过去 4 个星期里，您的健康或情绪不好在多大程度上影响了您与家人、朋友、邻居或集体的正常社会交往？**

①完全没有影响    ②有一点影响    ③中等影响    ④影响很大    ⑤影响非常大

**7、在过去 4 个星期里，您有身体疼痛吗？**

①完全没有疼痛    ②有一点疼痛    ③中等疼痛    ④严重疼痛    ⑤很严重疼痛

8、在过去 4 个星期里，您的身体疼痛影响了您的工作和家务吗？

- ①完全没有影响    ②有一点影响    ③中等影响    ④影响很大    ⑤影响非常大

## **您的感觉**

9、以下这些问题是关于过去 1 个月里您自己的感觉，对每一条问题所说的事情，您的情况是什么样的？

**(1) 您觉得生活充实：**

- ①所有的时间    ②大部分时间    ③比较多时间    ④一部分时间  
⑤小部分时间    ⑥没有这种感觉

**(2) 您是一个敏感的人：**

- ①所有的时间    ②大部分时间    ③比较多时间    ④一部分时间  
⑤小部分时间    ⑥没有这种感觉

**(3) 您的情绪非常不好，什么事都不能使您高兴起来：**

- ①所有的时间    ②大部分时间    ③比较多时间    ④一部分时间    ⑤小部分时间    ⑥没有这种感觉

**(4) 您的心理很平静：**

- ①所有的时间    ②大部分时间    ③比较多时间    ④一部分时间  
⑤小部分时间    ⑥没有这种感觉

**(5) 您做事精力充沛：**

- ①所有的时间    ②大部分时间    ③比较多时间    ④一部分时间  
⑤小部分时间    ⑥没有这种感觉

**(6) 您的情绪低落：**

- ①所有的时间    ②大部分时间    ③比较多时间    ④一部分时间  
⑤小部分时间    ⑥没有这种感觉

**(7) 您觉得筋疲力尽：**

- ①所有的时间    ②大部分时间    ③比较多时间    ④一部分时间  
⑤小部分时间    ⑥没有这种感觉

**(8) 您是个快乐的人：**

- ①所有的时间    ②大部分时间    ③比较多时间    ④一部分时间  
⑤小部分时间    ⑥没有这种感觉

(9) 您感觉厌烦:

①所有的时间      ②大部分时间      ③比较多时间      ④一部分时间

⑤小部分时间      ⑥没有这种感觉

10、不健康影响了您的社会活动（如走亲访友）:

①所有的时间      ②大部分时间      ③比较多时间      ④一部分时间

⑤小部分时间      ⑥没有这种感觉

## 总体健康情况

11、请看下列每一条问题，哪一种答案最符合您的情况？

(1) 我好象比别人容易生病:

①绝对正确      ②大部分正确      ③不能肯定      ④大部分错误      ⑤绝对错误

(2) 我跟周围人一样健康:

①绝对正确      ②大部分正确      ③不能肯定      ④大部分错误      ⑤绝对错误

(3) 我认为我的健康状况在变坏:

①绝对正确      ②大部分正确      ③不能肯定      ④大部分错误      ⑤绝对错误

(4) 我的健康状况非常好:

①绝对正确      ②大部分正确      ③不能肯定      ④大部分错误      ⑤绝对错误

### 12.2.2 SF-36 questionnaire

## SF-36 QUESTIONNAIRE

( 1992 -- Medical Outcomes Trust)

Patient Name: \_\_\_\_\_

Date: \_\_\_\_\_

1. In general, would you say your health is: (circle one)

Excellent      Very good      Good      Fair      Poor

2. Compared to one year ago, how would you rate your health in general now? (circle one)

Much better now than one year ago.

Somewhat better now than one year ago.

About the same as one year ago.

Somewhat worse than one year ago.

Much worse than one year ago.

3. The following items are about activities you might do during a typical day. Does your health now limit you in these activities? If so, how much? (Mark each answer with an **X**)

| ACTIVITIES                                                                                   | Yes,
limited
a lot | Yes,
limited a
little | No, not
limited
at all |
|------------------------------------------------------------------------------------------------------------|-----------------------------------|--------------------------------------|---------------------------------------|
| a. Vigorous activities , such as running, lifting heavy objects, participating in strenuous sports  |                                   |                                      |                                       |
| b. Moderate activities , such as moving a table, pushing a vacuum cleaner, bowling, or playing golf |                                   |                                      |                                       |
| c. Lifting or carrying groceries                                                                           |                                   |                                      |                                       |
| d. Climbing several flights of stairs                                                               |                                   |                                      |                                       |
| e. Climbing one flight of stairs                                                                    |                                   |                                      |                                       |
| f. Bending, kneeling or stooping                                                                           |                                   |                                      |                                       |
| g. Walking more than a mile                                                                         |                                   |                                      |                                       |
| h. Walking several blocks                                                                           |                                   |                                      |                                       |
| i. Walking one block                                                                                |                                   |                                      |                                       |
| j. Bathing or dressing yourself                                                                            |                                   |                                      |                                       |

4. During the past 4 weeks, have you had any of the following problems with your work or other regular daily activities as a result of your physical health? (Mark each answer with an **X**)

|                                                                                                      | YES | NO |
|------------------------------------------------------------------------------------------------------|------------|-----------|
| a. Cut down on the amount of time you spent on work or other activities                       |            |           |
| b. Accomplished less than you would like                                                      |            |           |
| c. Were limited in the kind of work or other activities                                       |            |           |
| d. Had difficulty performing the work or other activities (for example, it took extra effort) |            |           |

5. During the past 4 weeks, have you had any of the following problems with your work or other regular daily activities as a result of any emotional problems (such as feeling depressed or anxious)? (Mark each answer with an **X**)

|                                                                             | YES | NO |
|-----------------------------------------------------------------------------|------------|-----------|
| a. Cut down the amount of time you spent on work or other activities |            |           |
| b. Accomplished less than you would like                             |            |           |
| c. Didn't do work or other activities as carefully as usual          |            |           |

6. During the past 4 weeks, to what extent has your physical health or emotional problems interfered with your normal social activities with family, friends, neighbors or groups? (circle one)

Not at all      Slightly      Moderately      Quite a bit      Extremely

7. How much bodily pain have you had during the past 4 weeks? (circle one)

None      Very mild      Mild      Moderate      Severe      Very severe

8. During the past 4 weeks, how much did pain interfere with your normal work (including both work outside the home and housework)?

Not at all      A little bit      Moderately      Quite a bit      Extremely

9. These questions are about how you feel and how things have been with you during the past 4 weeks. For each question, please give the one answer that comes closest to the way you have been feeling. How much of the time during the past 4 weeks (Mark each answer with an X)

|                                                    | All of the time | Most of the time | A Good Bit of the Time | Some of the time | A little of the time | None of the time |
|----------------------------------------------------|-----------------|------------------|------------------------|------------------|----------------------|------------------|
| a. Did you feel full of pep?                       |                 |                  |                        |                  |                      |                  |
| b. Have you been a very nervous person?            |                 |                  |                        |                  |                      |                  |
| c. Have you felt so down in the dumps that nothing |                 |                  |                        |                  |                      |                  |
| d. Have you felt calm and peaceful?                |                 |                  |                        |                  |                      |                  |
| e. Did you have a lot of energy?                   |                 |                  |                        |                  |                      |                  |
| f. Have you felt downhearted and blue?             |                 |                  |                        |                  |                      |                  |
| g. Did you feel worn out?                          |                 |                  |                        |                  |                      |                  |
| h. Have you been a happy person?                   |                 |                  |                        |                  |                      |                  |
| i. Did you feel tired?                             |                 |                  |                        |                  |                      |                  |

10. During the past 4 weeks, how much of the time has your physical health or emotional problems interfered with your social activities (like visiting with friends, relatives, etc.)? (circle one)

All of the time      Most of the time      Some of the time      A little of the time  
None of the time

11. How TRUE or FALSE is each of the following statements for you?

|                                                         | Definitely true | Mostly true | Don't know | Mostly false | Definitely false |
|---------------------------------------------------------|-----------------|-------------|------------|--------------|------------------|
| a. I seem to get sick a little easier than other people |                 |             |            |              |                  |
| b. I am as healthy as anybody I know                    |                 |             |            |              |                  |

|                                       |  |  |  |  |  |
|---------------------------------------|--|--|--|--|--|
| c. I think my health is getting worse |  |  |  |  |  |
| d. My health is excellent             |  |  |  |  |  |

**Mycophenolate mofetil and new-onset systemic lupus  
erythematosus with high titer of anti-dsDNA antibody and  
without major organ involvement: A Randomized Clinical Trial**

## 1. List of abbreviations and definition of terms

|        |                                                |
|--------|------------------------------------------------|
| ACR    | American College of Rheumatology               |
| AE     | Adverse event                                  |
| ALT    | Alanine aminotransferase                       |
| AST    | Aspartate aminotransferase                     |
| BP     | Bodily pain                                    |
| CI     | Confidence intervals                           |
| CLIFT  | Crithidia luciliae immunofluorescence test     |
| CRF    | Case report form                               |
| CRP    | C-Reactive Protein                             |
| CTCAE  | Common Terminology Criteria for Adverse Events |
| DMARDs | disease-modifying antirheumatic drugs          |

|               |                                                                                                                    |
|---------------|--------------------------------------------------------------------------------------------------------------------|
| ELISA         | Enzyme-linked immunosorbent assay                                                                                  |
| ERA-EDTA      | European Renal Association-European Dialysis and Transplant Association                                            |
| ESR           | Erythrocyte sedimentation rate                                                                                     |
| EULAR         | European League Against Rheumatism                                                                                 |
| GCP           | Good Clinical Practice                                                                                             |
| GFR           | Glomerular filtration rate                                                                                         |
| GH            | General health                                                                                                     |
| HCQ           | Hydroxychloroquine                                                                                                 |
| HT            | Health transition                                                                                                  |
| IL-1          | Interleukin-1                                                                                                      |
| IL-2          | Interleukin-2                                                                                                      |
| IL-6          | Interleukin-6                                                                                                      |
| IgG           | Immunoglobulin G                                                                                                   |
| ICH-GCP       | International Conference on Harmonization-Good Clinical Practice                                                   |
| LLDAS         | Lupus low disease activity state                                                                                   |
| LN            | Lupus nephritis                                                                                                    |
| MCS           | Mental component summary                                                                                           |
| MH            | Mental health                                                                                                      |
| MHC           | Major histocompatibility complex                                                                                   |
| MMF           | Mycophenolate mofetil                                                                                              |
| MPA           | mycophenolic acid                                                                                                  |
| PCS           | Physical component summary                                                                                         |
| PF            | Physical functioning                                                                                               |
| PGA           | Physician's Global Assessment                                                                                      |
| SAE           | Serious Adverse Event                                                                                              |
| SD            | Standard deviations                                                                                                |
| SDI           | The Systemic Lupus International Collaborating Clinics (SLICC)/American College of Rheumatology (ACR) Damage Index |
| SELENA-SLEDAI | Safety of Estrogens in Lupus Erythematosus National Assessment-Systemic Lupus Erythematosus Disease Activity Index |
| SF-36         | Short form-36                                                                                                      |
| SF            | Social functioning                                                                                                 |
| SLE           | Systemic lupus erythematosus                                                                                       |
| SLEDAI-2000   | SLE Disease Activity Index-2000                                                                                    |
| SLICC         | The Systemic Lupus International Collaborating Clinics                                                             |
| RE            | Role emotional                                                                                                     |
| RP            | Role physical                                                                                                      |

|               |                                   |
|---------------|-----------------------------------|
| RR            | Relative risk                     |
| TNF- $\alpha$ | Tumor necrosis factor- $\alpha$   |
| UPCR          | Urine protein-to-creatinine ratio |
| VT            | Vitality                          |
| WBC           | White blood cell                  |

## 2. Introduction and background

Systemic lupus erythematosus (SLE) is a disease characterized by the elevation of producing large amounts of autoantigens and then causing the production of autoantibodies, of which anti-dsDNA antibody was important. Anti-dsDNA antibody could cause organ involvement including kidney, joint, skin and so on. Especially, it contributed to the pathogenesis of lupus nephritis (LN) through binding to antigens in renal cells or extracellular matrix, then triggering inflammatory activation and fibrotic processes. In addition, it has been reported that renal involvement was more frequent in patients with anti-dsDNA (+) (persistent positivity) compared with anti-dsDNA ( $\pm$ ) (initial positivity and subsequent negativity during disease course) or anti-dsDNA antibody(-) (persistent negativity).

It is considered that there are three types of SLE disease activity: relapsing-remitting, chronic activity, and long quiescence, with relapsing-remitting being the most common one. It has been reported that the level of anti-dsDNA antibody fluctuated with disease activity in SLE patients. Flares were preceded by the increase of anti-dsDNA antibody. In other words, an elevation of anti-dsDNA antibody could occur before SLE flares. A recent study reported that the prevalence of disease flares ranged from 13.0% to 15.7%. Therefore, it is urgently needed to investigate the early prevention of flares in SLE patients.

Treatment of SLE consists of the use of hydroxychloroquine (HCQ), prednisone, and disease-modifying antirheumatic drugs (DMARDs), among which mycophenolate mofetil (MMF) is an important one. MMF is the pro-drug of mycophenolic acid (MPA), which can inhibit inosine monophosphate dehydrogenase that is responsible for de novo synthesis of guanosine nucleotides. Besides, MPA can also regulate dendritic cell subsets to interrupt the harmful cascade of autoimmune disorders. Up to now, MMF is widely used as an inducement and maintenance treatment in LN.

It has also been reported that MMF could treat SLE patients with extra-renal involvement. Therefore, in this study, we aimed to explore the efficacy and safety of MMF on new-onset SLE patients with high titers of anti-dsDNA antibody and without major organ involvement and to observe its long-term effect.

### **3. Study outcomes**

#### **3.1 Primary Endpoint:**

The primary outcome was the proportion of patients who have flares (mild to moderate flares and severe flares) defined by modified SELENA-SLEDAI Flare Index (SFI)  at 96 weeks of follow-up.

The definition of mild to moderate flare is the fulfillment of one or more following items:

- 1) variation of SELENA-SLEDAI score  $\geq 3$  (but  $< 12$ );
- 2) new or worsening rashes, cutaneous vasculitis, nasopharyngeal ulcers, serositis, arthritis or fever caused by lupus;
- 3) increase in the dose of prednisone, but less than 0.5mg/kg/day;
- 4) increase of nonsteroidal anti-inflammatory drugs or HCQ;
- 5) Physician's Global Assessment (PGA) (0-3 scale)  $\geq 1$ .

Severe flare is defined as the fulfillment of one or more of the following items:

- 1) change in SELENA-SLEDAI score of more than 12;

- 2) new or worsening central nervous system involvement, vasculitis, nephritis, myositis, thrombocytopenia (platelet  $<60 \times 10^9/L$ ) or haemolytic anaemia (haemoglobin  $<70g/L$  or decrease in haemoglobin level  $>30g/L$ );
- 3) increased usage of prednisone (doubled in dosage or more than 0.5mg/kg/day);
- 4) added cyclophosphamide, azathioprine, methotrexate, mycophenolate mofetil or hospitalization because of lupus activity;
- 5) PGA  $>2.5$ .

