## **6.5 Methods of subject assignment**

Participants were randomly assigned (1:1) using blocks of four to receive either MMF (MMF group) or a control treatment (Control group). A statistician from the Clinical Trial Center of Ruijin Hospital, [name], who was masked to trial allocation generated the randomization sequences by a computer algorithm. Then, random numbers were written on the cards and packed in sequentially numbered envelopes that were opened when the patients were enrolled. [name] assigned patients to different groups according to the number on the card. Only Assessors were masked to the group allocation. Eligible subjects were recruited from the Department of Rheumatology and Immunology of Ruijin Hospital and the Department of Rheumatology and Immunology of the other two clinical centers.

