### **7.1.3 Establishment, preservation, and unblinding methods of trial drug codes and methods of unblinding in emergency situations**

Not applicable for this trial.

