## 4. Study design

In this study, we randomly assigned patients (1:1) to Control group and MMF group. Control group received treatment with HCQ (5mg/kg/day) and prednisone (0.5mg/kg/day); while MMF group received treatment with HCQ (5mg/kg/day) and prednisone (0.5mg/kg/day) plus MMF 500mg twice daily. The dose of MMF stayed the same unless a contrary or severe adverse event occurred.

Prednisone dose was tapered as follows:

Initial dose (0.5mg/kg/day) maintained for four weeks

[figure not shown]

tapered 5mg every two weeks till to 20 mg/day

↓

tapered 5mg every month

↓

gradually to 0.1-0.2mg/kg/day

The taper of prednisone doses was determined by the physicians according to the assessment of patients.

Notes:

- 1) Patients with severe flare were not involved in subsequent treatment plan, but they were still being followed up consistently until the end of the entire process.
- 2) Patients who met the criteria of severe flare were treated with increased doses of prednisone (more than 0.5mg/kg/day), immunosuppressive therapy or hospitalized for treatment according to the patients' condition and the physician's assessment.
- 3) Patients with mild to moderate flares continued to be followed up till the end of Week 96, and all flare episodes were recorded.
- 4) Patients with mild to moderate flares could increase the dose of prednisone (less than 0.5mg/kg/day) or nonsteroidal anti-inflammatory drugs.
- 5) For fever, rash, and arthritis, the dose of prednisone could be used at an initial dose of less than 0.5mg/kg/day, and following the assessment of symptoms, the dose could be increased to more than 0.5mg/kg/day if needed.
- 6) Any sign of kidney involvement (glomerular haematuria and/or cellular casts, proteinuria >0.5g/24hours (or spot urine protein-to-creatinine ratio (UPCR) >500mg/g), unexplained decrease in glomerular filtration rate (GFR)), renal biopsy was suggested to confirm the diagnose of LN. Results of renal biopsy were confirmed by a senior nephrologist ([name]). The treatment of LN was provided according to the European Renal Association-European Dialysis and Transplant Association (ERA-EDTA) guideline.
- 7) The treatment of other organ involvement was provided following the 2019 European League Against Rheumatism (EULAR) recommendation.

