## **8. Statistical procedures**

### **8.1 Randomization and masking**

Participants were randomly assigned (1:1) using blocks of four to receive either MMF (MMF group) or a control treatment (Control group). A statistician from the Clinical Trial Center of Ruijin Hospital, [name], who was masked to trial allocation generated the randomization sequences by a computer algorithm. Then, numbers were written on the cards and packed in sequentially numbered envelopes that were opened when the patients were enrolled. [name] assigned patients to different groups according to the number on the card. Assessors were masked to the group allocation. Eligible subjects were recruited from the Department of Rheumatology and Immunology of Ruijin Hospital and the Department of Rheumatology and Immunology of the other two clinical centers. Doctors were responsible for patient inclusion and regular follow-up assessments ([name], [name], [name], [name], and [name]). The assessment of patient flare was strictly based on the SELENA-SLEDAI Flare Index (including severe flare, and mild to moderate flare) rather than subjective decisions. Data analysts ([name] and [name]) were not involved in patient assessment and treatment, and they were masked to the group allocation.

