### **8.5 Primary outcome**

Flare proportion was defined as categorical variables, data were expressed in the form of frequency (percentages). The primary outcome was the proportion of patients with flares (including mild-to-moderate flares and severe flares) during follow-up. Safety of Estrogens in Lupus Erythematosus National Assessment-Systemic Lupus Erythematosus Disease Activity Index (SELENA-SLEDAI) Flare Index (SFI) was used for assessing disease flares in this trial. Pearson Chi-square or Fisher's exact tests were used to compare between-group differences. We first calculated the total flare rate, and then calculated mild-to-moderate flare rate and severe flare rate, respectively.

For the primary outcome, Bonferroni correction was used and two-sided at a significance level of 0.025. A more stringent statistical criterion was used. Relative risk (RR) was employed to compare the proportion of patients with the end point between MMF group and Control group. Severe flare-free survival proportion was estimated by using the Kaplan-Meier method in the intention to MMF group and Control group with a log rank test. Regarding patients who dropped out of the study, we collected all of the data during follow-up period. For patient who loss to follow-up, we did not collect the data for the subsequent time after lost to follow-up event. We used the ITT set for primary outcome calculation. All of the patients were included in the denominator. We estimated the severe flare-free survival proportion of the MMF group and Control group in both ITT and PP Set using the Kaplan-Meier method.

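### Severe-flare item 4 counts adding MMF, the randomized drug, as an event that in practice only control patients can have; the number of such events is unknown and no planned analysis would show it

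*Combined protocol and SAP*

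**What the plan says.** SAP 3.1 lists five severe-flare items and joins them with *or*: "Severe flare is defined as the fulfillment of one or more of the following items". Item 4 is "added cyclophosphamide, azathioprine, methotrexate, mycophenolate mofetil or hospitalization because of lupus activity". Neither flare definition mentions an increase in MMF dose.

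Both arms receive HCQ and prednisone; the MMF arm also receives MMF from randomization. SAP 4 and protocol 12.1 fix that dose: "The dose of MMF stayed the same unless a contrary or severe adverse event occurred".

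On masking, protocol 6.5 says "Only Assessors were masked to the group allocation". Protocol 7.1.3, on drug codes and unblinding, says "Not applicable for this trial". Under protocol 7.2.1 the doctor prescribes the drugs and the patient buys them at the outpatient pharmacy. Treating physicians and patients therefore know the allocation.

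On who assesses, protocol 7.3 gives regular follow-up assessment to masked observers. SAP 8.1 says assessors were masked, but also says "Doctors were responsible for patient inclusion and regular follow-up assessments". It adds that flares were scored by the index and not by subjective decision.

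SAP 8.5 defines the endpoint: "The primary outcome was the proportion of patients with flares (including mild-to-moderate flares and severe flares) during follow-up". The total rate is calculated first, then the mild-to-moderate and severe rates separately. The level is 0.025, and severe flare-free survival is estimated by Kaplan-Meier with a log-rank test.

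**The concern.** An endpoint component that contains the randomized treatment cannot work the same way in both arms. A control patient whose physician adds MMF for lupus activity becomes a severe flare by that act alone. A patient in the MMF arm with the same disease activity already takes MMF, so it cannot ordinarily be *added*, and raising its dose is not an item.

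Assessor masking does not remove this. The event is created by the unmasked physician's prescription, and a masked assessor who applies the index must still count it. Seeing that MMF was added also tells the assessor that the patient is a control. Scoring strictly by the index is no safeguard here, because this item is itself a treatment decision.

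The bias can run only in favour of MMF, and the 0.025 level does not correct a directional bias. Nor would the results reveal it. Table 3 of the SAP lists severe flares by manifestation, with no row for flares that rest on a medication change alone, and no analysis omits the component.

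**Working it through.** **1. The plan's own figure.** SAP 6 assumes overall flare rates of 10% (MMF) and 30% (control) and a two-sided unpooled Z test at 0.05. Exact binomial enumeration with 58 per arm gives power 0.8036, and actual alpha 0.0568 at a common rate of 30%. Both match the plan. For dropout, 58 / (1 − 0.10) = 64.4, rounded up to 65 per arm. The sample-size arithmetic is sound and is not the issue.

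**2. Which components are asymmetric.**

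| Severe-flare component (SAP 3.1) | Control arm | MMF arm |
|---|---|---|
| Item 1, score change | can occur | can occur |
| Item 2, organ or blood involvement | can occur | can occur |
| Item 3, prednisone increase | can occur | can occur |
| Item 4, cyclophosphamide, azathioprine or methotrexate added | can occur | can occur |
| Item 4, hospitalization | can occur | can occur |
| Item 4, **MMF added** | can occur | not in practice |
| Item 5, PGA | can occur | can occur |

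A patient in the MMF arm who stopped and restarted MMF might arguably qualify, but no rule says so.

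**3. What the asymmetry could do to the severe-flare test.** The documents give neither a severe-flare rate nor a number of flares met by added MMF alone, so both are assumptions.

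- n = 65 per arm (SAP 6) and two-sided level 0.025 (SAP 8.5).
- Assumed true severe-flare rate of 15% in both arms, that is, no treatment effect.
- k = average number of controls counted as severe only because MMF was added. Each adds 1/65 = 1.5 percentage points, so the control rate is 0.15 + k/65.

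The test is Pearson's chi-square, z = (p_C − p_M) / √[p̄(1 − p̄) · 2/65], significant when |z| ≥ 2.241. The rejection probability is the sum of Bin(x; 65, 0.15) · Bin(y; 65, 0.15 + k/65) over all pairs (x, y) that are significant.

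| k | Control rate | Chance of a significant result |
|---|---|---|
| 0 | 15.0% | 2.4% |
| 1 | 16.5% | 2.8% |
| 2 | 18.1% | 4.0% |
| 3 | 19.6% | 6.1% |
| 5 | 22.7% | 13.1% |
| 6 | 24.2% | 18.0% |

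Nearly all of the excess favours MMF: at k = 3, false claims in that direction rise from 1.2% to 6.0%. The assumed base rate matters only moderately. At k = 3 the chance is 7.2%, 5.6% and 4.9% for base rates of 10%, 20% and 30%.

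**4. Total flare rate.** The mild-to-moderate items include a score change of at least 3, new or worsening rash or arthritis, a smaller prednisone increase, and PGA of at least 1. A control given MMF for lupus activity would usually meet one of these already. Adding MMF then moves the patient from mild-to-moderate to severe and leaves the total unchanged.

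**The case against.** The strongest objection is that the plan leaves little room for flares that rest on added MMF alone. Protocol 7.1.1 and 8.1 and SAP 4 describe "immunosuppressive therapy or hospitalized for treatment according to the patients' condition and the physician's assessment" as management for patients who already meet severe-flare criteria. For mild-to-moderate flares they list only a limited prednisone increase or anti-inflammatory drugs. Treatment of nephritis follows nephritis, which is already item 2. A route remains through treatment of other organ involvement, but that is real disease. This stands: such events may be few, and with one or two of them the error rate barely moves. It does not make the number zero, because the choice rests on an unmasked physician's assessment and item 4 needs no other item to be met.

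A second objection is that a patient in the MMF arm who needs escalation can also become a severe flare, through another listed agent, prednisone or hospitalization. This also stands. It confines the asymmetry to one component, so a reader should not infer that the endpoint as a whole is constructed differently in the two arms.

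A reader might also infer that the enrolling doctors, unmasked, classify the flares, so that SAP 8.1 contradicts protocol 7.3. The documents do not establish this. SAP 8.1 also says assessors were masked, and with names removed one cannot tell whether the listed doctors are the masked observers. The two texts are ambiguous and need to be reconciled. The documents also never call the trial open-label; it is unmasked for physicians and patients, with masked assessors.

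**Conclusion.** The asymmetry is real and follows from the endpoint text. One component of severe flare can in practice be triggered only in the control arm, by an unmasked prescription, and any resulting bias favours MMF. It bears on the separate severe-flare comparison at 0.025 and on severe flare-free survival.

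Its size is unknown. Under the assumed 15% base rate, the false-positive chance runs from 2.4% with no such patients to 6.1% with three and 18.0% with six. These are illustrations under assumptions, not estimates for this trial.

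It is tempting to say that the rule inflates the primary total flare rate, or to express a few such patients as a share of the planned 20-point difference. The documents support neither. That difference (30% against 10%) concerns any flare, and most patients given MMF for lupus activity would already be counted as having a flare.

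This should be fixed: the plan as written leaves no way to learn whether the effect was nil or decisive, and the remedy is cheap.

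**What to change.** - Record and report, by arm, which item or items triggered each flare. Show separately the flares that rest on added MMF alone.
- Pre-specify a sensitivity analysis of severe flare, total flare and severe flare-free survival in which a flare met only by added MMF is not counted as severe. The patient is reclassified by the remaining items, and the severe-flare date becomes the first date, if any, on which another severe item is met.
- Optionally, add a supportive analysis on the clinical items, scored by masked assessors without medication data. It should not replace the sensitivity analysis, because it also drops items that are neutral between the arms. Adding MMF dose increases to item 4 would achieve little, because the dose is fixed.
- Reconcile protocol 7.3 with SAP 8.1 and state whether masked observers classify flares.

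The cost is one extra derivation from data already collected: medication is recorded at every visit (protocol 7.6, SAP 12). The sensitivity analysis will have slightly fewer severe-flare events. It may also miss a later severe flare that the added MMF prevented, so it should be read beside the main analysis. No patient's treatment changes.
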